***Personnel/ Staffing***

There will be 8 field interviewers employed for the cohort component. They will work in teams of two, with two teams each covering Barabanki and Unnao Districts. These four teams will work in both the districts. Field teams will be coordinated and supervised by the Nutrition Project Coordinator with assistance from the Field Coordinator. [name] and his colleagues at KGMU will provide technical assistance to the Project Coordinator and her cohort team.

Each field team will require 2-3 days to identify and enroll eligible women in each AWC, so one team will be able to cover approximately 16-18 AWCs per month. Using 2 field teams, recruitment and enrollment is estimated to take 3 months. We expect approximately 5-6 births per AWC. Because follow-up data collection activities will begin during the enrollment period, a third team will be needed in each district during that time (3 months). Therefore, two temporary workers will be hired in each district during the enrollment period so 3 teams will be available. Each temporary worker will be paired with a permanent field worker to form the data collection teams. One pair of permanent team members will start the follow-up visits as soon as team gets the delivery information. Rest, two pairs of one temporary and one permanent team member will continue with house-listing and enrollment.

One data editor, data entry personnel, programmer/ data manager will be employed. They will be based in central location (i.e. Lucknow) and work with Project Coordinator for programming, data, editing, entry and cleaning. They will also provide logistic support during trainings.

***Follow-up***

All the pregnant women considered eligible at the time of recruitment/ enrollment and have consented to enroll in the study will be followed-up (FUP) postpartum. These recruited women and their infants will be continued to followed until study ends or the child is 18 months of age. If the index child expires follow-up will be terminated after the visit at which the child’s death is ascertained. FUP visits will be continued with the child and it’s caregiver even if the mother expires. If the participating woman leaves the catchment area, she will be coded as ‘moved away’ and her FUP visits will be discontinued. For a woman who is out of village temporarily, follow-up visits will be continued every three months until the women returns or it is confirmed that she has moved permanently. If any visit is ‘missed’ due to unavailability of mother; first two sections of the previous questionnaires will be filled during subsequent visit. At a given visit, no more than two questionnaires will be filled although day-7 questionnaire can be filled at any given visit. Women enrolled in the study can also discontinue their participation and drop out at any follow-up visit.

FUP visits will be scheduled to take place at the critical period immediately after programmatic exposure occurs. Therefore, first FUP visit is scheduled at seven days after child birth as programmatic interventions are scheduled in first seven days after delivery. After first visit at day-7, later visits will be scheduled every three months from the date of birth of index child (child being followed-up). A birth calendar will be generated on the basis of every child’s date of birth. This will help in scheduling FUP visit dates to avoid manual or calculation mistakes in scheduling these visits by the team members.

All the visits completed within 15 days of scheduled date of visit will be considered on-time. Every Saturday of the week, teams will come to the office and submit a form that will report the number of AWC surveyed, number of houses listed, number of pregnant women identified and number of FUP visits completed. A weekly plan for next week’s visits will also be submitted to coordinate and track the movement of the teams by project/ field coordinator.

***Tracking & supervision***

At enrollment, teams will fill a register for all the enrollments done in each AWC for both the districts separately. In these registers, pregnant women’s address, LMP, expected date of delivery and other contacts will be recorded by AWC name. These registers will be updated by each team everyday. This will provide a data base to cover all possible deliveries and avoid missing them since it will help teams to cover all the expected deliveries in a given AWC even if mother/ respondent doesn’t make a phone call to the Lucknow office. Each AWC will be re-visited at least once in every 15 day to identify the pregnancy.

**Data collected**

Questionnaires will be filled with the help of mother and only in cases where mother is not alive, caretaker of the child will help filling the questionnaires.

Figure above shows the categories in which data will be collected at different age ranges/ time interval for every child. Since women has been enrolled at various stages of pregnancy, the range is from 6 completed months to 9 months, there is chance of missing the information on interactions with service providers, advices given and health services utilization for the interviews completed at earlier stages of pregnancy. Therefore, we will be repeating the information on advice given and health services utilization during pregnancy while filling Day-7 questionnaires.

Anthropometry

- weight
- length

Breastfeeding/ infant feeding practices

Day-7

- initiation
- current breast-feeding

Month-6

- Breastfeeding
- Introduction of complementary foods

Health Advice

At each interview, we ask about health advice received using both unprompted and prompted questions.

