***Recruitment***

Eligible pregnant women will be recruited simultaneously at the time of house-listing. One of the team will take oral consent and conduct the interview and take height and weight measurements of the index mother. If there is more than one pregnant women in the household, both will be enrolled for the study. Teams will give one calendar to the respondent (eligible enrolled pregnant woman) with the central office phone numbers to make a call within 24 hours of delivery.

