***Eligibility criteria***

A comprehensive house-listing will be maintained. All the pregnant women identified for cohort enrollment will be queried to ascertain eligibility.

Women will be considered eligible if:

1. They are at least 24 weeks (completed 6 months/ 180 days) pregnant on the day of house-listing. Gestational age will be assessed by recall of the date of the last menstrual period (LMP) and by asking completed months of pregnancy. In case woman is unsure of her LMP; teams will be provided with local festival calendar that will help in recalling the tentative date of LMP.
2. They intend to remain in the program area (same village) during the duration of the study. Women who are visiting their parents’ home should be excluded unless it is determined that their permanent residence is also within the cohort sample area so they can be followed up at that alternate location. Women who report that they intend to visit their parents’ home for delivery or during the postpartum period can still be enrolled as long as their visit is not intended to be long-term (more than 3 months) and someone in their family is willing to inform our study team about the birth regardless of a woman’s location.
3. Pregnant daughters who are permanently (more than one year) staying with their parents will be considered eligible.

The study will be explained to the women, and if she agrees to participate will be considered eligible. Women will be recruited into the cohort subject to their consent to participate.

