***Data collected in Cohort:***

| TIME PERIOD | 6-9 mo | 6-9 mo | 7 day | 7 Day | 3 mo | 3 mo | 6 mo | 6 mo | 9 mo | 9 mo | 12-24 mo | 12 mo | 15  mo | 18 mo |
| --- | --- | --- | --- | --- | --- | --- | --- | --- | --- | --- | --- | --- | --- | --- |
| PROGRAM  COMPONENTS | Dietary advice,  SN, TT2,  100 IFA,  Rest and workload, Birth plan |  | Bfd. < 60 min.  Exclusive bfdg,  Colostrum  Feeding, prob.  Immun,  Maternal diet,  Rest & workload, SN |  | Exclusive bfdg,  Immun,  Maternal diet,  Rest,  SN |  | Continued on-demand bfdg,  Weaning, Quantity & quality,  Feeding during illness,  SN,  Maternal diet,  Rest,  SN |  | Continued on-demand bfdg,  Quantity & quality,  SN, Feeding during illness,  SN,  Vitamin A at 9 months,  Maternal diet,  Rest,  SN |  | Continued on-demand bfdg,  Quantity & quality,  SN, Feeding during illness,  SN,  Iron tablets  Vitamin A (18 mo)  Maternal diet,  Rest,  SN |  |  |  |
| EVALUATION |  |  |  |  |  |  |  |  |  |  |  |  |  |  |
| Vital Status of Mother & Infant |  |  |  | X |  | X |  | X |  | X |  | X | X | X |
| ♀Socio-demographic information |  | X |  |  |  |  |  |  |  |  |  |  |  |  |
| ♀ Health Advice Given During Pregnancy |  | X |  | X |  |  |  |  |  |  |  |  |  |  |
| ♀ Health Service Utilization During Pregnancy |  | X |  | X |  |  |  |  |  |  |  |  |  |  |
| ♀ Birth Preparedness |  | X |  |  |  |  |  |  |  |  |  |  |  |  |
| ♀ Maternal Diet |  | X |  |  |  | X |  | X |  | X |  |  |  |  |
| ♀ Rest and Workload |  | X |  |  |  | X |  | X |  | X |  |  |  |  |
| ♀ Anthropometry |  | X |  |  |  |  |  |  |  |  |  |  |  |  |
| Delivery |  |  |  | X |  |  |  |  |  |  |  |  |  |  |
| Health advice given |  |  |  | X |  | X |  | X |  | X |  | X |  | X |
| Breast-feeding Initiation |  |  |  | X |  | X |  |  |  |  |  |  |  |  |
| Infant Feeding Practices |  |  |  | X |  | X |  | X |  | X |  | X | X | X |
| Feeding and Care During Infant Morbidity |  |  |  | X |  | X |  | X |  | X |  | X | X | X |
| Repeat Dietary Recall in 24-hr Child Feeding |  |  |  |  |  |  |  |  |  |  |  | X |  | X |
| Immunization |  |  |  |  |  | X |  | X |  | X |  | X | X | X |
| Child Anthropometry |  |  |  | X |  | X |  | X |  | X |  | X | X | X |

1. **Training and standardization:**
   1. **Interviews**
2. **dietary recall**
3. **advice questions (prompted/ un-prompted, probing protocols, decision making for coding)**
   1. **Anthropometry**
4. **Validation sub-studies**
   1. **Hemo-cue**
   2. **24 hour dietary recall**

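### Birth preparedness is asked once, at 6 to 9 months' gestation, and is left out of the Day-7 repeat that the protocol uses to cover the rest of pregnancy

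*Protocol*

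**What the plan says.** Under *Recruitment* (Protocol, Component 2) the pregnancy interview is tied to listing: "Eligible pregnant women will be recruited simultaneously at the time of house-listing". Under *Eligibility criteria* the lower limit is set: "They are at least 24 weeks (completed 6 months/ 180 days) pregnant on the day of house-listing". Gestation at interview is therefore whatever it happens to be on the listing day, at or above that limit.

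*Data collected* acknowledges the spread, "Since women has been enrolled at various stages of pregnancy, the range is from 6 completed months to 9 months", and its consequence for early interviews: "there is chance of missing the information on interactions with service providers, advices given and health services utilization". The remedy follows: "we will be repeating the information on advice given and health services utilization during pregnancy while filling Day-7 questionnaires".

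The schedule under *Data collected in Cohort* agrees with that text. Two pregnancy rows carry a mark at both enrolment and Day-7: "Health Advice Given During Pregnancy | | X | | X" and "Health Service Utilization During Pregnancy | | X | | X". Birth Preparedness carries one mark in the whole study, at enrolment. Among the programme components for the 6-9 month pregnancy period, the same schedule lists a birth plan.

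**The concern.** The protocol identifies a truncation problem and applies its remedy to two of the domains asked at the enrolment interview. Birth preparedness is at least as exposed as those two. Arrangements for a birth build up until delivery, so a question put three months before delivery catches only part of what a woman will have done.

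At stake is a process indicator for one programme component. A reading taken at mixed gestations is neither preparedness by delivery nor preparedness at a fixed point in pregnancy, and it falls short of the former. If the same fraction is missed in both districts, the absolute difference between arms shrinks by that fraction, and a real programme effect on this item looks smaller than it is. This needs no imbalance between the districts.

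**Working it through.** **Step 1. The schedule, row by row** (Protocol, *Data collected in Cohort*).

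| Row asked at the pregnancy interview | 6-9 months' gestation | Day-7 | Later marks |
| --- | --- | --- | --- |
| Health advice in pregnancy | X | X | none |
| Health service use in pregnancy | X | X | none |
| Birth preparedness | X | – | none |
| Rest and workload | X | – | 3, 6, 9 months |
| Maternal diet | X | – | 3, 6, 9 months |

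Of these rows, only birth preparedness has no second reading at all. By the protocol's own range, the pregnancy time left after the interview runs from about 0 to 3 months per woman.

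**Step 2. Illustration of the size.** The documents give no figure for this, so what follows rests on declared assumptions.

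- Gestation at interview, G, is uniform from 180 days (the eligibility limit) to 280 days (assumed term).
- Among women who eventually prepare, the day of preparation, T, is uniform from day s to day 280 and independent of G. The start day s is assumed to be 140, 180 or 210.
- The share recorded at enrolment is P(T ≤ G) = E[max(G − s, 0)] / (280 − s).

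Mean G is (180 + 280)/2 = 230, so on average 280 − 230 = 50 of the last 100 days lie after the interview. Then:

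- s = 140: (230 − 140)/(280 − 140) = 90/140 = 0.64
- s = 180: (230 − 180)/(280 − 180) = 50/100 = 0.50
- s = 210: P(G > 210) × mean excess / 70 = (70/100) × (35/70) = 0.35

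The eligibility criterion equates 24 weeks with 180 days, but 24 × 7 = 168. With a floor of 168 the three shares become 84/140 = 0.60, (100/112) × (50/100) = 0.45 and (70/112) × (35/70) = 0.31. The message is the same.

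**Step 3. Effect on the arm difference.** Let p1 and p0 be the true proportions prepared by delivery and f the share recorded, equal in both arms. The recorded difference is f·p1 − f·p0 = f(p1 − p0). With f between 0.35 and 0.64, the absolute difference is scaled down to 35% to 64% of its true size. If the programme also brings preparation forward, f is larger in the intervention arm and this simple scaling no longer holds.

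**Step 4. Could gestation at listing differ between districts?** Suppose mean gestation differed by 14 days, with G uniform on 180–266 in one district and 194–280 in the other (means 223 and 237). The recorded shares would be:

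- s = 140: 83/140 = 0.59 against 97/140 = 0.69
- s = 180: 43/100 = 0.43 against 57/100 = 0.57
- s = 210: (56/86) × (28/70) = 0.26 against (70/86) × (35/70) = 0.41

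That is a shift of 10 to 15 points among eventual preparers with no true difference. Is 14 days plausible by chance? The SD of a uniform on 180–280 is 100/√12 = 28.9 days. With 400 women per arm, the standard error of the difference in means is 28.9 × √(2/400) = 2.04 days, ignoring clustering by Anganwadi centre. Fourteen days is 14/2.04, about 7 standard errors.

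**The case against.** **A spurious programme effect.** A reader might infer that because listing proceeds centre by centre over about three months in two non-randomised districts, differences in gestation at listing will appear as a programme effect. The documents do not support this. Both districts share the same eligibility floor, list every household, invite all third-trimester women, and have 81 centres each. Listing spread over time does not by itself shift gestation, because each listing takes whoever has then passed the limit. The 14-day scenario would leave one district with no woman below 194 days and the other with none above 266, and nothing in the protocol suggests that. Balance is not guaranteed, but imbalance is not shown.

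**Rest, workload and maternal diet.** A reader might also infer that these are asked only once. They are not: both are asked again at 3, 6 and 9 months postpartum, and once is true only within pregnancy. If they are asked as current practice, which cannot be told because the questionnaires are not shown, the enrolment answer truncates nothing. It is a snapshot at varying gestation. The schedule's Day-7 programme column does include "Rest & workload, SN", but that column describes what the programme delivers around birth. It does not show that late-pregnancy practice should have been asked at Day-7.

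**Low consequence.** Birth preparedness is not sized in Tables 4.1 or 4.2, is not named among the cohort measures in Figure 1, and a birth plan is not in the pregnancy row of Table 1. This stands and sets the severity.

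**Unseen instruments.** The Day-7 Delivery section may capture some arrangements. That is possible, but the schedule gives no Day-7 mark to birth preparedness, and the text names only two repeated domains.

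**The remedy has its own weakness.** A Day-7 answer is given after the delivery is known. *Follow-up* allows the Day-7 form to be completed at any visit, and eligible women may be away for up to three months, so recall is not always short. This also stands, and it is why the enrolment reading should be kept.

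**Conclusion.** The point holds for birth preparedness. The protocol states the reason for a Day-7 repeat and does not apply it to an item that accumulates to delivery and is asked only once. Preparedness by delivery is understated in both districts, and so is the absolute arm difference if the timing of preparation is similar in the two arms. Under the stated uniform distributions, 35% to 64% of eventual preparers would be recorded. That range illustrates the size and is not an estimate from trial data.

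For rest and workload and for maternal diet, the most that can be said is that the single pregnancy reading is taken at varying gestation. A bias between arms is conditional on a difference in gestation at listing that the documents do not show. Severity is minor.

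**What to change.** Add the birth-preparedness items, worded as what had been arranged by the time of delivery, to the Day-7 questionnaire beside the two domains already repeated. Keep the enrolment reading, and report preparedness by delivery from the Day-7 answer. Record the date on which the Day-7 form is completed, and examine late forms separately.

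For pregnancy items that stay at enrolment only, including rest and workload and maternal diet, adjust the arm comparison for gestational age at interview. This needs no new data, since the last menstrual period is already recorded, and its detail can sit in the analysis plan. Adjustment cannot recover preparation made after the interview. For birth preparedness, only a later question can do that.

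The cost is a few more questions at a visit already scheduled, and one covariate. The downside is postpartum recall coloured by knowledge of the delivery, and longer recall when the form is completed at a later visit.

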***Data collected in Cohort:***

| TIME PERIOD | 6-9 mo | 6-9 mo | 7 day | 7 Day | 3 mo | 3 mo | 6 mo | 6 mo | 9 mo | 9 mo | 12-24 mo | 12 mo | 15  mo | 18 mo |
| --- | --- | --- | --- | --- | --- | --- | --- | --- | --- | --- | --- | --- | --- | --- |
| PROGRAM  COMPONENTS | Dietary advice,  SN, TT2,  100 IFA,  Rest and workload, Birth plan |  | Bfd. < 60 min.  Exclusive bfdg,  Colostrum  Feeding, prob.  Immun,  Maternal diet,  Rest & workload, SN |  | Exclusive bfdg,  Immun,  Maternal diet,  Rest,  SN |  | Continued on-demand bfdg,  Weaning, Quantity & quality,  Feeding during illness,  SN,  Maternal diet,  Rest,  SN |  | Continued on-demand bfdg,  Quantity & quality,  SN, Feeding during illness,  SN,  Vitamin A at 9 months,  Maternal diet,  Rest,  SN |  | Continued on-demand bfdg,  Quantity & quality,  SN, Feeding during illness,  SN,  Iron tablets  Vitamin A (18 mo)  Maternal diet,  Rest,  SN |  |  |  |
| EVALUATION |  |  |  |  |  |  |  |  |  |  |  |  |  |  |
| Vital Status of Mother & Infant |  |  |  | X |  | X |  | X |  | X |  | X | X | X |
| ♀Socio-demographic information |  | X |  |  |  |  |  |  |  |  |  |  |  |  |
| ♀ Health Advice Given During Pregnancy |  | X |  | X |  |  |  |  |  |  |  |  |  |  |
| ♀ Health Service Utilization During Pregnancy |  | X |  | X |  |  |  |  |  |  |  |  |  |  |
| ♀ Birth Preparedness |  | X |  |  |  |  |  |  |  |  |  |  |  |  |
| ♀ Maternal Diet |  | X |  |  |  | X |  | X |  | X |  |  |  |  |
| ♀ Rest and Workload |  | X |  |  |  | X |  | X |  | X |  |  |  |  |
| ♀ Anthropometry |  | X |  |  |  |  |  |  |  |  |  |  |  |  |
| Delivery |  |  |  | X |  |  |  |  |  |  |  |  |  |  |
| Health advice given |  |  |  | X |  | X |  | X |  | X |  | X |  | X |
| Breast-feeding Initiation |  |  |  | X |  | X |  |  |  |  |  |  |  |  |
| Infant Feeding Practices |  |  |  | X |  | X |  | X |  | X |  | X | X | X |
| Feeding and Care During Infant Morbidity |  |  |  | X |  | X |  | X |  | X |  | X | X | X |
| Repeat Dietary Recall in 24-hr Child Feeding |  |  |  |  |  |  |  |  |  |  |  | X |  | X |
| Immunization |  |  |  |  |  | X |  | X |  | X |  | X | X | X |
| Child Anthropometry |  |  |  | X |  | X |  | X |  | X |  | X | X | X |

1. **Training and standardization:**
   1. **Interviews**
2. **dietary recall**
3. **advice questions (prompted/ un-prompted, probing protocols, decision making for coding)**
   1. **Anthropometry**
4. **Validation sub-studies**
   1. **Hemo-cue**
   2. **24 hour dietary recall**

1. AWC is a focal point of service delivery of ICDS package of services at the village or community level, covering a population of 1000 population . The Anganwadi is managed by an AWW, who belongs to the same community [↑](#footnote-ref-2)
2. Block Level Resource Mapping (BLRM) is a key tool for participatory planning and monitoring of key nutrition and health issues. Key government staff and partners map the information at block level for analyzing trends and identifying the problems and develop solutions to improve the service delivery. Action plan with clear roles and responsibilities for both ICDS and Health departments is chalked out. [↑](#footnote-ref-3)
3. Nutrition and Health Day (NHD) is defined as a “set day, happening at least once a month, when take-home rations are distributed, an ANM visits the AWC and offers immunization and/or antenatal care services”. [↑](#footnote-ref-4)
4. Change Agents (CA) is an active, interested member of the community who acts as a promoter and monitor of health and nutrition practices in the neighborhood (one per 15-20 families) and who counsels families to promote positive health behaviors on a voluntary basis. [↑](#footnote-ref-5)
5. Community Based Monitoring System (CBMS) consists of a set of tools that are evolved through a participatory process that enables communities to monitor their own nutrition and health practices as well as the facilitates service providers to target and improve coverage of services. [↑](#footnote-ref-6)
